### Methods: assignment of interventions (for controlled trials)

#### Allocation sequence generation

Communities will be randomly grouped into two stratification factors—region (Central vs. Top End) and size (small vs. large). These will be further assigned randomly into five different 6-monthly HfLI start dates with transition from control to HfLI being in sequences 0111111, 0011111, 0001111, 0000111 and 0000011 (0 = control and 1 = HfLI).

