**Fig. 1 Fig1:**
[figure not shown]
Design matrix (actual dates inserted prospectively) with dates (month/year) proposed for unblinding and training commencement

**Table 1 Tab1:** Definitions applied to the Hearing for Learning Initiative SW-CRT (see Fig. 1)

Cluster (unit of randomisation)	18 Northern Territory Aboriginal communities (clusters) allocated 2:4:4:4:4 to 5 start dates (sequences). Stratified by NT region (Top End or Central) and size (large or small)
Cluster period (a grouping of observations by time of measurement and cluster)	7 including baseline (i.e. 1 baseline, 5 training or transitions, and 6 Initiatives). Each cluster period has a duration of 6 months
Number of sequences	5 sequences. The order of sequence is 0111111, 0011111, 0001111, 0000111 and 0000011 (0 = control and 1 = initiative)
Number of clusters randomised to each sequence	Variable (2 in 1 sequence and 4 in 4 sequences)
Number of time periods	7 including baseline
Duration of time between each step	6 months
Transition period	3-month training period

**Table 2 Tab2:** Participant timeline (actual dates to be inserted prospectively)

Community numbers	Unblind	Lead-in phase (within control periods)	Cross-over dates (transition periods)	Integration and employment commences (intervention periods)
1–2	Month 1 TP 1	Months 1 to 10* TP1-2	Months 10 to 12 TP2	Month 1 TP3
3–6	Month 10* TP2	Months 10 TP2 to month 4 TP3	Months 4 to 6 TP3	Month 7 TP4
7–10	Month 4 TP3	Months 4 to 10 TP4	Months 10 to 12 TP4	Month 1 TP5
11–14	Month 10 TP4	Month 10 TP4 to month 4 TP5	Months 4 to 6 TP5	Month 7 TP6
15–18	Month 4 TP5	Months 4 to 10 TP6	Months 10 to 12 TP6	Month 1 TP7

*Anticipated delay due to COVID-19 ** TP: 6-monthly TimePeriod (Fig 1)

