### Secondary outcomes—integration and employment

Integration measures will be Ear Health Facilitator workplace attendance, punctuality, data collection and data entry skills (Redcap, PCIS or Communicare), attendance at supervisor meetings, case load and attendance during outreach service visits (audiologist and surgical outreach).

Subgroup analyses will be by child age group (0 to 3, 4 to 5, over 5 years of age) and by the five Priority groups recommended by the 2020 OM Guidelines.

Sensitivity analyses will compare data from control and HfLI intervention periods with or without the integration period.

Participant timeline (Table 2 and Fig. 1)
Control periods: For all communities, the control period begins in year one at unblinding of the first allocated cross-over date (January 2020). For each community, the control period ends at commencement of their training and includes the lead-in phase.Lead-in phase: For each community, the period between unblinding of their allocated cross-over date to commencement of training (3 to 6 months)Transition period: The period between commencement and completion of training (3 months).Integration phase: The period between completion of training and end of integration into the health service (3 months).Intervention period: The period between completion of training (or end of Integration phase in sensitivity analysis) and end of TimePeriod 7.

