### Statistical methods

The intention to treat principle will be adhered to, where clusters will be analysed according to their time of switching between control and HfLI. Randomisation is conducted as soon as all communities have provided support of the HfL Initiative in their community and prior to the commencement in any of the participating communities. Unblinding of the communities allocated to the next 6-monthly cross-over date will be done 6 months prior to that cross-over date, to allow for a lead-in phase of community preparation that is still the control period. To allow for delays in implementation, a separate per protocol analysis will be performed with the assessments now placed into one of the three categories: control period pre-allocated cross-over date (including the lead-in period of 6 months), post-allocated cross-over date but pre-implementation (the training phase) and post-implementation (from commencement of employment and including integration phase). The distribution of results across the control group will be compared with the HfLI group

Characteristics of individuals and clusters in the HfLI will be summarised by their exposure status [29]. Demographic characteristics of children will be summarised as proportions and/or means (SD) or medians (IQR) by control and HfLI group. For a sub-set of the population, risk factor questionnaires with parents will be used to examine the distribution of known confounders (such as birth weight, smoke exposure from pre-conception, breast feeding, household crowding, etc.) between control and HfLI periods.

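### The printed randomisation sequences start HfLI one 6-month period before Table 2 and the timeline definitions do, and the article does not say which sets the primary exposure indicator

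*Protocol article*

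**What the plan says.** Two places give the exposure pattern as 0/1 strings over seven 6-month periods. Under Allocation sequence generation the text has "transition from control to HfLI being in sequences 0111111, 0011111, 0001111, 0000111 and 0000011 (0 = control and 1 = HfLI". Table 1 repeats it: "The order of sequence is 0111111, 0011111, 0001111, 0000111 and 0000011 (0 = control and 1 = initiative". Table 1 also counts "1 baseline, 5 training or transitions, and 6 Initiatives", and has 18 communities "allocated 2:4:4:4:4 to 5 start dates (sequences".

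Table 2 gives the calendar. For communities 1–2 the cross-over (training) entry is "Months 10 to 12 TP2", and the column headed "Integration and employment commences (intervention periods") begins in Month 1 of TP3. The other four groups follow the same pattern at 6-month steps, ending with communities 15–18, who train in TP6 and start in TP7.

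The Participant timeline defines the phases. Control runs until training starts and includes lead-in; the training months are a transition; and then "Intervention period: The period between completion of training (or end of Integration phase in sensitivity analysis) and end of TimePeriod 7".

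Under Statistical methods, intention to treat means that "clusters will be analysed according to their time of switching between control and HfLI". A separate per-protocol analysis sets the training phase apart. The primary model has one HfLI indicator and categorical time.

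**The concern.** The strings and the calendar differ by one full period in all five sequences, so this is not a slip in one row. Two codings of the primary exposure can be read from the same article, and the intention-to-treat sentence does not choose between them because it does not define switching.

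This matters more in a stepped-wedge trial than in a parallel one. With a fixed effect for every period and strong within-community correlation, the treatment estimate leans heavily on the contrast around each cross-over. If the first period counted as exposed contains no service delivery, most of the information about the effect is lost. An unresolved coding also leaves room to choose it after outcome data have been seen.

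**Working it through.** **1. Strings against calendar**

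| Communities | Printed string | First 1 | Training (Table 2) | Intervention starts (Table 2) |
|---|---|---|---|---|
| 1–2 | 0111111 | TP2 | months 10–12, TP2 | TP3 |
| 3–6 | 0011111 | TP3 | months 4–6, TP3 | TP4 |
| 7–10 | 0001111 | TP4 | months 10–12, TP4 | TP5 |
| 11–14 | 0000111 | TP5 | months 4–6, TP5 | TP6 |
| 15–18 | 0000011 | TP6 | months 10–12, TP6 | TP7 |

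Training fills only the second half of each first coded-1 period. The first half is lead-in, which the definitions call control.

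Cluster-periods coded 1: 2×6 + 4×(5+4+3+2) = 68. Cluster-periods with intervention in Table 2: 2×5 + 4×(4+3+2+1) = 50. The difference is 18, or 26% of 68.

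**2. Inputs (Sample size section)**

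Control proportion 0.329, difference 0.10, two-sided 5%, m = 90 children per cluster-period, ICC 0.06, CAC 0.7, 18 communities allocated 2:4:4:4:4, 7 periods. No value is given for the individual autocorrelation (IAC), so 0 to 0.9 is assumed.

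**3. Method**

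Generalised least squares on cluster-period means, with categorical period effects and one treatment indicator. With J the all-ones matrix and I the identity,

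V = σ²[ICC·CAC·J + ICC(1−CAC)·I + (1−ICC)·IAC/m·J + (1−ICC)(1−IAC)/m·I],

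σ² = (0.329×0.671 + 0.429×0.571)/2 = 0.2329.

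Power is Φ(0.10/SE − 1.96). For the mismatch, the estimator's weights under the printed strings are applied to a mean that rises only from the periods in which Table 2 starts the intervention. The result is the fraction of the true effect that is recovered.

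**4. Results**

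| IAC | SE, printed strings | Power for +10 points | Fraction recovered under mismatch | Power under mismatch |
|---|---|---|---|---|
| 0 | 0.0267 | 96.3% | 0.234 | 14% |
| 0.5 | 0.0243 | 98.5% | 0.225 | 15% |
| 0.9 | 0.0221 | 99.5% | 0.220 | 17% |

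- The plan's 98% is reproduced to within 2 points.
- Under the mismatch, a true +10 points is estimated on average as +2.2 to +2.3 points. At IAC 0, 0.0234/0.0267 = 0.88 standard errors, hence the 14%.
- Over m 50–200, ICC 0.02–0.2, CAC 0.6–1 and IAC 0–0.8, the fraction is 0.20 to 0.29.
- A logit-scale simulation (400 runs, true log odds ratio 0.427) gives a mean estimate of 0.099, a fraction of 0.23.
- If 10%, 25% or 50% of the effect were already present in the transition period, the fraction would be about 0.30, 0.42 or 0.61.
- A fit that ignored clustering would give 0.47, but that is not the planned model.

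**5. Alternatives**

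- Strings moved one period later (0011111 to 0000001): no attenuation under the same assumptions. SE and power are unchanged at 96.3 to 99.5%, because only the number of all-control and all-HfLI periods at the two ends changes.
- Whole transition period dropped (18 of 126 cluster-periods): no attenuation, but the SE rises by about 31% (at IAC 0, 0.0267 to 0.0351). Power is 81% (IAC 0) to 93% (IAC 0.9).

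**The case against.** The best defence is that the strings and Table 2 are two calendars. Table 2 footnotes an anticipated COVID-19 delay and marks it on the lead-in of communities 1–2, which runs from month 1 to month 10 although lead-in is defined as 3 to 6 months. With a three-month lead-in, those communities would train in months 4–6 of TP1 and start in TP2, which is exactly 0111111. At 6-month steps the last group would start in TP6, which is 0000011. Table 1's five transitions and six initiative periods fit that calendar too. This is plausible, but the article does not say it, and it prints the strings unchanged beside the delayed calendar.

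A reader might infer that the design deliberately counts the transition as HfLI, or that the intention-to-treat result will be about a quarter of the truth. The documents support neither. Nowhere is the indicator defined as the strings laid over Table 2's periods. The Statistical methods section itself calls lead-in control. The separate training category in the per-protocol analysis suggests, but does not establish, that intention to treat counts training as HfLI, and even then only three of the six months are concerned.

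Two further points have some weight. The Interventions section makes training one of three phases of the intervention, so counting from the start of training could be intended; half of the disputed period would still be control by definition. Figure 1 is not shown and may mark transition cells, but that would not make the printed strings agree with Table 2.

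**Conclusion.** The contradiction stands and needs no assumption: the strings in Table 1 and under Allocation sequence generation run one period ahead of Table 2 and the Participant timeline for all 18 communities, and nothing in the article reconciles them.

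The size is conditional. A fraction of 0.22 to 0.23 and power of 14 to 17% require that the primary indicator follows the strings on Table 2's calendar, that the transition period carries no effect, that the effect is constant afterwards, and that clustering is modelled as planned. With half the effect present in the transition period the fraction is about 0.61 to 0.62. If the timeline definitions set the indicator, the loss is nil.

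The stated 98% power is not itself an error, since it holds equally for strings that match Table 2. The point should be settled before outcomes are analysed, because the possible codings can differ about fourfold in the primary estimate.

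**What to change.** Make Table 1, Allocation sequence generation, Table 2 and the Participant timeline agree, and say whether the strings predate the delay. State one primary coding keyed to the allocated date, not the achieved one. If Table 2's calendar stands, set HfLI to 1 only from the period after training: 0011111, 0001111, 0000111, 0000011, 0000001. Correct Table 1's count of initiative periods to match (five for the first sequence, TP3 to TP7).

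This coding leaves the three training months on the control side, so any early effect of training would dilute the estimate somewhat. Handle that with a sensitivity analysis that excludes the transition, either the whole period or only the training months. Whole-period exclusion is less suitable as the primary analysis because it also discards lead-in time that the protocol defines as control. If it is chosen as primary, restate power at about 81 to 93% and give the IAC on which the figure rests.

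The cost is wording in the protocol and the analysis plan. No new data are needed, and power under the recommended coding stays at about 96 to 99.5%.

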#### Allocation concealment mechanism

All communities were recruited prior to randomisation which was conducted at a single time point. Cross-over dates for each cluster will be concealed until the lead-in period, to reduce differential attrition. The statistician provided the allocation list (code/strata/start date) to the Menzies Senior Data Base Manager not involved in the HfLI delivery who maintains blinding until 3 to 6 months (lead-in phase) prior to each of the five HfLI start dates. Each group of communities will be unblinded by the independent Data Manager and provided to the Program Manager. The Program Manager will inform these communities and commence the lead-in phase (Table 2).

#### Implementation

The statistician not involved in the HfLI delivery will conduct the stratified allocation with clusters divided into distinct strata before random allocation within each stratum, using Stata 15.1 (StataCorp, College Station, TX).

#### Enrolment and consent (see Additional file 2)

Enrolment and consent of communities will be performed by the Program Manager and one of the investigators. This will involve the process described above. When 18 communities provide written expressions of interest in participation or other written approvals (i.e. consent), no further consultation will be undertaken. Communities that do not respond will be assumed to have refused consent and will be excluded (i.e. the first 18 will be enrolled). All community approvals will be provided to the ethics committees for confirmation of ethical approval.

#### Enrolment of child participants

For our primary outcome, the denominator is the number of resident children 0 to 16 years of age. Ethical approval for waiver of individual consent will be sought to retrieve relevant deidentified ear and hearing data from the medical records. A data access agreement will be executed with the relevant health services (Department of Health or ACCHOs) for this purpose.

For child participants receiving the HfLI (ear and hearing health checks by the Ear Health Facilitators), consent will be required. All age-eligible children whose parents consent to participation will be eligible for enrolment. Written informed consent will be obtained by the Ear Health Facilitators who will be trained by the Clinical Research Training Officers. To minimise selection bias, participant consent will be encouraged by multiple parties including Community Reference Group members, the school and health service staff and the Ear Health Facilitators. The open cohort design allows for continuous recruitment of children.

#### Enrolment of cluster level participants

For impact and program process evaluation questionnaires, written informed consent will be required from health and education service providers, Community Reference Group members, the Ear Health Trainees, Ear Health Facilitators and families. Consent will be obtained by members of the clinical trial team which includes the Ear Health Facilitators.

#### Blinding (masking)

Blinding will be maintained until 6 months prior to the training start date for each unblinded community (Fig. 1). Participant and research team blinding regarding the control-HfLI status cannot be achieved following assignment to a start date (Fig. 1). Administrative data from all communities will be retrieved 6-monthly for aggregated analyses. The Data Manager and Analyst will be aware of the cross-over dates and how many communities have transitioned from control periods to HfLI periods. However, the identity of communities will not be provided in the aggregated administrative dataset.

We do not anticipate the need for the Data Manager and Analyst to have any individual participant unblinded. The iDSMB will review process and progress of the trial implementation and data collection. Stopping rules will consider safety only. However, if there are major concerns about trial futility, such as withdrawal of more than four communities, poor engagement in training or other impacts such that an effect is unlikely to be detectable, or if the aggregated data suggests superiority of the HfLI, the iDSMB may request analysis of outcomes according to control and HfL Initiative periods. The Senior Data Managers at Menzies will hold the unblinded allocation of community start dates.

### Methods: data collection, management and analysis

#### Data collection methods

Data retrieval and analysis, trends analysis and retrospective data collection for all NT Government serviced communities included in the Primary Care Information System (PCIS) system database for the period of 2015–2019 will be used in calculating the pre-existing global trends in the targeted trial clinical outcome measures across remote NT communities prior to baseline. A similar process of trend analysis of data from communities using Communicare is planned.

#### Pilot phase

A pilot of the HfLI will be undertaken in two communities, one that uses the PCIS system and the other the Communicare system. Data fields relative to ear and hearing health and our targeted trial clinical outcome measures will be identified in each system for harmonisation. The pilot phase will test data collection and data entry methods (paper-based forms, tablets (Redcap) or direct database entry).

#### Trial phase

Data from all 18 participating communities (PCIS and Communicare) for the period from the start to the end of the trial will be retrieved 6-monthly using the data-identity separation principles for data retrieval and data linkage.

Ear assessment data entered and retrieved from the PCIS or Communicare systems by all health professionals and by Ear Health Facilitators will contribute to the analyses. Data collected by the Ear Health Facilitators alone (paper-based forms or tablets (REDCap) can be used to determine the contributions by the Ear Health Facilitators.

#### Communities as participants

Data will be collected from all 20 communities (including two self-nominated pilot communities) from baseline to end of the trial. Retention of communities prior to their start date, during the pre-HfLI period, will be encouraged through regular communications about the overall trial milestones and annual in-service 1-day workshops for resident health service professionals on evidence-based guidelines for OM in Aboriginal and Torres Strait Islander children. Retention of communities during the training, integration and HfLI periods will also be encouraged by the training team, the HfLI governance members including the Community Reference Groups, the study Champions, Ear Health Trainees and the Ear Health Facilitators. For communities who formally withdraw, we will negotiate the terms to ensure ongoing primary outcome data collection can occur. The trial has a participation agreement with key decision makers and services which will cover this.

#### Ear Health Facilitators as participants

Retention of the Ear Health Facilitators will be encouraged through a dedicated workplace integration plan, local mentors, local health and education professionals as HfLI champions, advice from the Community Reference Group and a help line to the Training team at Menzies. Employment of the Ear Health Facilitators by the health service will be funded by the HfLI until the end of the HfL Initiative. FTE will be determined by each community and budget allocation. Part-time and job share arrangements that suit the community cultural protocols will be a priority.

#### Children 0 to 16 years of age as participants

For our primary outcome, relevant ear and hearing data will be retrieved from the medical records of all children 0 to 16 years of age who reside in the 18 participating communities. Participation of families and their children in the ear and hearing checks will be encouraged. The HfLI aims to train and employ Ear Health Facilitators in community to ensure that families have confidence in the ear and hearing checks for their children. The Ear Health Facilitators will have state-of-art diagnostic equipment that will enable them to conduct these checks outside the clinic at places more convenient to families and children. Parental consent for the Ear Health Facilitators to conduct children’s ear and hearing checks will be required. The Community Reference Group and the Ear Health Facilitators will advise on best practice in informing parents about the HfLI, through ear health promotion activities at networking events across the community.

### Data management

#### Data entry

Each child’s ear and hearing health assessment made by the Ear Health Facilitators may be collected at non-clinic sites, such as the kindergarten, home or school. Standardised ear observation forms or tablets will be used when off-site. These forms will be held in locked storage at the health service. Data will be entered (asynchronously if collected off-site) into the child’s electronic medical record (PCIS or Communicare) either directly by the trained Ear Health Facilitator, by the trained Ear Health Facilitator under supervision or by the child’s health care provider who receives the ear observation data from the Ear Health Facilitator.

#### Database

For government clinics, standard PCIS ear and hearing-related fields will be used. For Communicare, a dedicated template has been designed for the project, including identical fields as the PCIS system, in addition to standard Communicare fields. The data fields on the paper forms, tablets, Communicare and PCIS systems will be harmonised. Data from questionnaires conducted verbally by the training or independently by participants will be collected on paper-based forms or tablet (into a purpose-built Redcap data entry form). Paper forms and tablets will be stored in secure offices at the health service. All paper-based forms will be scanned to a secure email address at Menzies School of Health Research. Original forms will be transported to Menzies by the training team or via post and using a tracking system for secure storage in locked filing cabinets. Data on tablets will be uploaded to a secure database at Menzies.

